### 4.2 Type of therapy assignment

Participating hospitals will be randomized into two sequences before the start of the study. The randomization ratio for the two study arms is 1:1. It is intended to blind patients, i.e., no patient learns whether or not his or her treating physician receives a telephone consultation. Blinding of study physicians is not possible. The change from the intervention group to the control group or from the control group to the intervention group (cross-over) will take place for each hospital individually after inclusion of the 17th patient or after one year at the latest. The aim is to include a total of 30 patients per hospital.

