### 4.3 Number and type of comparison groups

Two parallel groups will be formed. The first group represents the intervention group, in which randomized hospitals receive a non-requested telephone consult by a clinical infectious disease specialist when SAB is detected. The second group represents the control group, in which SAB is recorded and patients are followed up, but in which no nonrequested telephone consultation by a clinical infectious disease specialist occurs when SAB is detected. After inclusion of 250 patients, but no later than 12 months after initiation of inclusion, crossover of comparison groups occurs. That is, hospitals initially randomized to

the intervention group will now receive no unsolicited telephone consults when a patient with SAB is included. These patients will also be recorded and followed up. The hospitals that were initially randomized to the control group will then receive a non-solicited telephone consult when a patient with SAB is reported.

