## 5 Participating study centers

This study will include at least 15 of the up to 39 hospitals participating in AlertsNet 2.0 and a total number of 500 patients. Participating hospitals will be randomized into 2 groups with 2 sequences: A-B or B-A. Here, A represents the intervention and B the control group ("standard of care"). During the intervention, treating physicians at participating hospitals will receive unsolicited telephone consults recommending an evidence-based set of interventions to treat SAB (11).

The condition for participation here is that the laboratory to which a hospital sends its microbiological samples is connected to AlertsNet2.0. With regard to the IT concept, reference is made to the AlertsNet2.0 application.

Qualification of the participating centers or treating physicians beyond routine clinical work is not necessary. The telephone consultation is carried out by a clinical infectiologist or a physician with sufficient infectiological experience. There is no minimum number of patients to be included. The change of the groups takes place individually for each center after inclusion of the first 17 patients or after 12 months at the latest.

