## 9.5 Statistical analysis

Differences in the primary end point, 30-day all-cause mortality, are determined confirmatorily within the framework of a generalized linear mixed model (GLMM). This was specified in more detail by Reich et al (25) and also forms the basis of the case number calculation. This model is suitable to represent the dependence structure by the clusters and the period effects for a dichotomous outcome variable, where the null hypothesis of no treatment effect can be rejected if the two-sided p-value of the Wald test statistic for the fixed effect *group* can be rejected at the two-sided significance level  $\alpha=5\%$ . The confirmatory test is performed according to the ITT principle, with missing endpoint data in included patients replaced by multiple imputation. Further sensitivity analyses of the primary endpoint are "worst case" imputations as well as analyses in the PP collective. In addition, the *a priori* defined subgroups center, gender and age groups (quartiles) of the patients will be analyzed stratified. For these analyses as well as for the adequate statistical analyses of the secondary endpoints, which will also be performed within GLMM, no multiplicity adjustment is planned.

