## 48 1.2 Introduction of a wash out phase

49 In addition to the specifications made in the study protocol (version 1.07 of 18.05.2016)  
 50 regarding randomization and inclusion of patients in the intervention and control groups, a  
 51 one-month wash-out phase will be introduced between the end of the intervention phase  
 52 (after the inclusion of 15 patients in one institution) and the start of the control phase (before  
 53 the inclusion of 15 additional patients in the institution who are educated but do not receive a  
 54 consil). This phase is intended to ensure that knowledge of improved treatment strategies  
 55 gained during the intervention phase approaches pre-study routines, allowing clearer  
 56 differentiation between outcomes the intervention and control phases. Accordingly, no wash  
 57 out phase is required between the end of the control phase and a subsequent intervention  
 58 phase.

59

60

61

---

62 [name].med. **[name]**, Head of the study Date

63

64

65

---

66 **[name]**, M.D., Deputy Study Director Date

67

68

69

70 *[name].med. **[name]**, Biometrician*

Date

71

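### The center-stratified subgroup analysis in Section 9.5 mixes the treatment effect with the period effect, because each hospital switches only once

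*Protocol*

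**What the plan says.** Section 9.5 (Statistical analysis) makes three statements that bear on this point.

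- On subgroups: the "defined subgroups center, gender and age groups (quartiles) of the patients will be analyzed stratified". Center is thus a pre-specified stratification factor on the same footing as gender and age.
- On multiplicity, for these and the secondary analyses: "no multiplicity adjustment is planned".
- On the primary generalized linear mixed model: "This model is suitable to represent the dependence structure by the clusters and the period effects for a dichotomous outcome variable". Period effects are therefore something the protocol intends to account for.

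The design is set out in Section 5: "Participating hospitals will be randomized into 2 groups with 2 sequences: A-B or B-A", with A the intervention and B the control. The switch comes "after inclusion of the first 17 patients or after 12 months at the latest". Section 4.2 has the same individual trigger, while Section 4.3 has a study-wide one: "After inclusion of 250 patients, but no later than 12 months after initiation of inclusion, crossover of comparison groups occurs". The amendment adds that a "one-month wash-out phase will be introduced between the end of the intervention phase" and the control phase, and none in the other direction. These passages differ on what triggers the switch, but all of them give each hospital exactly one intervention phase and one control phase.

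**The concern.** A stratified analysis fits or tabulates the group contrast separately in each stratum. That is possible for gender and age, because every stratum contains patients from hospitals of both sequences. It fails for center. A single hospital has one sequence, so knowing the phase is the same as knowing the group. Nothing inside the hospital can distinguish an effect of the consult from a change in mortality between its first and second phase. The hospital random effect would also have only one level within such a stratum.

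The risk lies in interpretation. A shift in mortality between phases would push A-B hospitals in one direction and B-A hospitals in the other. The resulting table could be read as hospitals where the consult helps and hospitals where it harms, when it shows only the sequence each was assigned. The asymmetric wash-out shows that the protocol itself expects the order of phases to matter.

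**Working it through.** **Inputs**

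- 15 centers, on average 15 patients per phase (Section 9.3; Section 4.5 also gives 15 evaluable per phase). The protocol's total reproduces: 15 × 2 × 15 = 450.
- Planning mortality: 0.25–0.5 intervention, 0.5–0.7 control, relative risk about 0.5 (Section 9.3).
- Lower mortality quoted elsewhere: 25% hospital mortality (Section 1.3). Halving it gives 12.5%.
- Period effect: no figure in the protocol. Odds ratios of 1.25, 1.5 and 2 are assumed for illustration.

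**Step 1: what a center contrast estimates.** On the logit scale, let α be the hospital's baseline, β the treatment effect and π the change from phase 1 to phase 2.

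- A-B hospital: intervention = α + β, control = α + π, contrast = β − π.
- B-A hospital: intervention = α + β + π, control = α, contrast = β + π.

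The mean of the two contrasts is ((β − π) + (β + π)) / 2 = β. That is how the pooled analysis recovers the treatment effect, and why one hospital alone cannot.

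**Step 2: identifiability by column rank of the design matrix (15 centers, 8 A-B and 7 B-A)**

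| Model | Parameters | Rank |
|---|---|---|
| One center: intercept + phase + group | 3 | 2 |
| Pooled, primary type: center + period + group | 17 | 17 |
| Pooled: center + common period + fixed center-specific group effects | 31 | 30 |
| Pooled: center + period + group + gender + gender-by-group + gender-by-period | 20 | 20 |

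The third row has 15 + 1 + 15 = 31 parameters but only 15 × 2 = 30 center-phase cells. A fixed center-by-group interaction therefore does not rescue the analysis. The second row shows that the primary comparison is sound, and the fourth that gender is estimable.

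**Step 3: size of the distortion with no treatment effect (β = 0)**

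| Assumed period OR | Group OR in A-B hospitals | Group OR in B-A hospitals |
|---|---|---|
| 1.25 | 1/1.25 = 0.80 | 1.25 |
| 1.5 | 1/1.5 = 0.67 | 1.5 |
| 2 | 1/2 = 0.50 | 2.0 |

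**Step 4: information per center if there is no period effect.** Power of the two-sided Fisher test at 5%, summed over all outcomes of two binomials with n = 15 each:

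| Control vs intervention | Expected deaths | Power |
|---|---|---|
| 25% vs 12.5% | 3.75 vs 1.875 | about 6% |
| 50% vs 25% | 7.5 vs 3.75 | about 16% |
| 70% vs 35% | 10.5 vs 5.25 | about 32% |

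The last two rows are pairs inside the Section 9.3 ranges with relative risk 0.5. For 50% vs 25%, the odds ratio is (0.25/0.75)/(0.5/0.5) = 0.33. The standard error of its logarithm is √(1/(15·0.5·0.5) + 1/(15·0.25·0.75)) = 0.79, so the 95% interval runs from about 0.07 to 1.56.

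**The case against.** The strongest reply is that the effect within a center is not unidentifiable in every model. It can be estimated if no period effect is assumed, if center effects are random around a common effect with a common period effect, or if a common calendar-time effect is fitted and hospitals switch at different dates, as Sections 4.2 and 5 allow. A staggered example with 24 monthly terms has full rank (53 of 53), against 52 of 53 when all hospitals switch together. This stands, and it limits the wording: the confounding is conditional on allowing a period effect. But each route adds an assumption or borrows from other hospitals, so none of them is the stratified analysis that Section 9.5 states. Individual switching also means that phases need not share calendar dates, so one common shift is a simplification.

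It can also be said that Section 9.5 does not promise center-specific p-values and that a purely descriptive table by hospital would do no harm. That is fair as to the table, but the text lists center as a subgroup to be analysed like the others.

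Three stronger readings are tempting and not supported:

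- **The primary result is compromised.** It is not. The confirmatory test uses both sequences, and its model has full rank.
- **False positives are very likely.** A reader might count 15 center, 2 gender and 4 age tests and compute 1 − 0.95^21 = 0.66. That needs 21 independent tests of exact size 5%. The three factors re-divide the same patients, and Fisher's test at 15 vs 15 has an actual size of about 0.9% to 1.8% at common rates of 12.5% to 50%. Over 15 independent center tests this gives roughly 12.8% to 23.5%.
- **Omitting interaction tests for gender and age is an error.** The protocol neither specifies nor excludes them, and such detail commonly sits in a statistical analysis plan, which is not shown here.

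**Conclusion.** The point holds for center only. As written, the center-stratified contrast estimates β − π in A-B hospitals and β + π in B-A hospitals, so it cannot deliver what a reader would take from it unless the period effect is zero. An assumed period odds ratio of 1.5 alone would make the two kinds of hospital look opposite (0.67 and 1.5). How large the period effect will be is unknown; the protocol gives no figure. If it is nil, the center results are unbiased but nearly uninformative, with power of about 6% to 32% depending on the mortality assumed.

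The finding rests on one switch per hospital, which every version of the switch rule in the protocol shares, and on the protocol's own wish to model period effects. It is minor: these are supportive analyses, openly unadjusted for multiplicity, and the confirmatory test is untouched.

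**What to change.** In Section 9.5, remove center from the list of stratified subgroups and keep gender and age. Add one sentence: between-hospital differences in the effect will be explored by a random group-by-hospital effect added to the primary model, with its period term retained, and shown as its estimated variance or as shrunken hospital estimates, labelled exploratory.

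The cost is one sentence in the protocol, with no further data and no burden on patients. There are two limits to state with the results. With about 15 hospitals the variance of the random group effect will be imprecise. And with only two cells per hospital, a period change peculiar to one hospital would still be absorbed into that variance, so it should not be read as pure treatment heterogeneity.

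Optionally, the statistical analysis plan could add group-by-gender and group-by-age terms fitted on all patients. That is a suggestion, not a correction.

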## 9.6 Presentation of the results

It is planned to publish the data in a peer-reviewed scientific journal after completion of the data analysis. An interim analysis or a publication of data before completion of the study, also in the context of a congress presentation, is not planned. The presentation of data will follow the guidelines of the CONSORT statement (<http://www.consort-statement.org>) (27).

In all publications or presentations of the project, it must be explicitly stated that the financial support is provided by the Federal Ministry of Health (BMG), grant number 01EO1502.

Regarding the rights and obligations of the authors involved, the publication guidelines for authors in medical journals according to the recommendations of the American Medical Association (<http://jama.jamanetwork.com/public/instructionsforauthors.aspx>) must be followed.

# 10 Data Management

## 10.1 Patient Identification List

Each study center maintains a patient identification list in which patient identification numbers (automatically generated SIC) are linked to participants' full patient names, date of birth, gender, and date of study enrollment. This list is used to enable subsequent identification of participating patients.

The patient identification list must be treated confidentially and must not leave the study center. It must be archived for **at least ten years** after the end of the study. In addition, the participation of the persons concerned in the study is noted in the respective patient file.

## 10.2 List of responsibilities

For each study center, a signature list including the name, function in the study, study-related activity and abbreviation of the responsible persons is filed in the study center folder and in the central trial folder. With this overview, other persons involved in the clinical trial are also designated with their names, signature and abbreviations as well as their responsibilities and authorities.

## 10.3 Data collection/documentation forms

### 10.3.1 Data collection

To achieve the study objective, it is necessary to collect and process medical data of the study participants. Data collection is performed by the SUPPORT study nurse at the study centers participating in the study, based on their documentation systems.

Source data in the sense of ICH guideline E6 are defined as all routinely collected data and laboratory reports as well as special CRFs for the documentation of the study. The majority of the data to be collected is routinely collected and entered directly into the regular patient record.

### 10.3.2 Documentation forms

A documentation sheet for the study is provided to the study centers. The actual documentation of the data will be done by the SUPPORT study nurse at the study centers directly from the medical record. The following data should be entered into the CRF:

#### 10.3.2.1 Study inclusion -Patient identification number

- Inclusion criteria according to **section 6.1**
- Exclusion criteria according to **section 6.2**
- Presence of the declaration of consent
- Patient inclusion (no/yes), date and time if applicable.
- Group Allocation

#### 10.3.2.2 Demographic data

- Age
- Sex
- Height
- Weight
- Date of hospital admission
- Reason for recording
- Stay in other inpatient facilities

#### 10.3.2.3 Resistance of the *S. aureus* isolate of the 1st blood culture.

#### 10.3.2.4 Origin of infection

- ambulatory
- health-care associated
- nosocomial

#### 10.3.2.5 Infection focus

- Intrathoracic infection
- Urogenital/renal infections
- Infection of the central nervous system
- Bone and joint infections
- Infections of the cardiovascular system

- 566 -HNO/oropharyngeal infections
- 567 -Intraabdominal infections
- 568 -Skin and soft tissue infections
- 569 -Postoperative wound infections
- 570 -Flexure tube as suspected source of infection
  
- 571 10.3.2.6 Characteristics of blood culture
- 572 -Date of blood culture collection
- 573 -Location of blood culture collection
- 574 -Presence of foreign bodies or prostheses
- 575 -Further positive blood cultures
- 576 -Detection of other bacteria
  
- 577 10.3.2.7 Presence of SIRS criteria
  
- 578 10.3.2.8 Organ dysfunction within 7 days of 1st positive blood culture.
- 579 -Acute encephalopathy
- 580 -Thrombocytopenia
- 581 -Arterial hypoxemia
- 582 -Renal dysfunction
- 583 -Metabolic acidosis
  
- 584 10.3.2.9 Septic shock within 7 days after 1. positive blood culture.
  
- 585 10.3.2.10 Severity of SAB
- 586 -uncomplicated
- 587 -complicated
  
- 588 10.3.2.11 PITT score on the day of blood culture collection (24).
  
- 589 10.3.2.12 Charlson comorbidity index (23)
  
- 590 10.3.2.13 Recommended measures/implementation of the recommended measures
- 591 -Time
- 592 -Follow-up blood cultures
- 593 -Focus remediation
- 594 -Transesophageal echocardiography
- 595 -other proposed measures
  
- 596 10.3.2.14 Laboratory values on the day of the positive blood culture
- 597 - Creatinine
- 598 -Creatinine Clearance
- 599 -Bilirubin
- 600 -Lactate
- 601 -CRP
- 602 -PCT
- 603 -ALAT
- 604 -ASAT
- 605 -AP
- 606 -leukocytes
- 607 -platelets
- 608 -neutrophil granulocytes
- 609 -Ferritin

#### 10.3.2.15 Patient status at hospital discharge

- ICD 10 Main diagnosis
- Place of discharge
- Mortality date
- Discharge date
- ITS stay during hospitalization.
- Complications
- Progression of the SAB

#### 10.3.2.16 Complications

- Contrast agent allergy when performing a CT
- Esophageal rupture during transesophageal echocardiography.
- Pneumothorax during catheter reimplantation
- Death during surgical focal rehabilitation.
- Acute renal failure under vancomycin.
- Acute renal failure under aminoglycosides.
- Acute liver failure during flucloxacillin therapy.
- Acute liver failure during rifampicin therapy.
- Antibiotic Allergy
- occurrence of *Clostridium difficile enteritis*.
- other complications

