## 7 Course of studies

### 7.1 Detailed study process

Information about a microbiological blood culture result *positive* for *S. aureus* is automatically reported to the SUPPORT team via the AlertsNet infrastructure (Electronic Blood Culture Registry, EBCR). However, data management is done separately. The system sends a fax to the treating hospital with the patient's clinical name, -year of birth, *subject identification code* (SIC) and microbiological findings. The study center at the UKJ, which is informed at the same time, does not receive any clear name information but only the information of a SAB detection in a specific institution and the automatically generated case code (SIC). The study center contacts the study physician at the clinical institution and, based on the relevant positive microbiological findings and using the SIC, asks for the patient to be included in the study. If the patient agrees to participate in the study after being informed by the study physician, the signed consent form is faxed to the study center. Only with this fax does the study center thus receive clear name information on the SAB-positive patient. Thereupon, for patients of the intervention arm, the telephone consultation with the treating physician is performed and subsequently the consultation is confirmed by fax (incl. therapy proposal). For patients in the control group (no infectious disease consultation), the two aforementioned steps are omitted. After inclusion in the study, only the informed consent form is faxed to the study center. A consultation is not performed for these patients.

The SUPPORT study nurse documents the data of the study patients pseudonymously in the CRF as soon as possible during her on-site visits. After 30 and after 90 days, a follow-up call is made to the patients by the study center. The contact details for this are recorded separately in the consent form (**Figure** and **Section 14.2**).

[figure not shown]

\*EBCR: Electronic Blood Culture Registry

325

326 **Figure:** Flow chart for the SUPPORT study.

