## 8 Adverse events/complications

### 8.1 Adverse events

SUPPORT is not a study in the sense of the AMG. All recommended measures and medications are routinely used in everyday clinical practice. Specific adverse events due to the intervention (telephone consultation) are not expected, since the telephone consultation only suggests treatment options that the treating physician can implement. Complications of the recommended and implemented diagnostic and therapeutic measures (e.g. esophageal perforation after transesophageal echocardiography, contrast medium- or vancomycin-induced renal insufficiency, pneumothorax when changing a CVC, etc.) are documented. ) are documented.

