### 8.2 Possible complications and/or risks

Complications are defined as all events that are or could be related to the therapeutic and diagnostic measures recommended in the infectious disease consultation. These include complications that may occur as a result of the medications (intolerances to the recommended antibiotic or contrast agent when performing contrast computed tomography) or as a result of medically interventional complications, such as those that may occur during abscess cleavage or transesophageal echocardiography. The drugs to be recommended are approved for the treatment of *S. aureus* bacteremia by the "European Medicines Agency" (EMA). The medical measures to be recommended belong to routine clinical examinations, about the risks of which the treating physician is obliged to inform the patient before the examination. Therefore, for the SUPPORT study, there are no specific risks for the participating patients that exceed the clinical routine.

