### 8.3 Recording and documentation of complications

Complications are recorded over a period of 90 days after inclusion in the study. In case of doubt, the study outpatient clinic should be contacted by telephone. In case of death, the

cause of death should be documented. Unexpected, previously unknown complications for which a causal relationship with the recommended measures cannot be ruled out will be reported to the study participants within one week.

All complications will be documented in the patient's chart and later recorded in the CRF by the SUPPORT study nurse.

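### Complications are defined by what the consult recommended, so read literally the definition has no referent in the control arm and cannot support the safety comparison named in the synopsis

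*Protocol*

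**What the plan says.** **Objective.** The synopsis (protocol 1.4) gives the primary objective as efficacy, measured by 30-day mortality, and safety, both relative to care without telephone consults. Section 3.1 states the objective as mortality alone. Sections 3.2 and 9.1 list no complication endpoint, and 9.5 describes no complication analysis.

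**Definition.** Section 8.2: "Complications are defined as all events that are or could be related to the therapeutic and diagnostic measures recommended in the infectious disease consultation". Section 8.1 says that what is documented is "Complications of the recommended and implemented diagnostic and therapeutic measures", and one of its examples is "contrast medium- or vancomycin-induced renal insufficiency". Section 8.3 limits the rapid reporting of unexpected events to those for which a "causal relationship with the recommended measures cannot be ruled out".

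**Window.** Section 8.3: "Complications are recorded over a period of 90 days after inclusion in the study".

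**Control arm.** Section 7.1, on control patients: "A consultation is not performed for these patients".

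**Listed items.** Section 10.3.2.16 contains four renal or liver failure items, each tied to a drug: "Acute renal failure under vancomycin", the same for aminoglycosides, "Acute liver failure during flucloxacillin therapy", and the same for rifampicin. It also lists contrast allergy, antibiotic allergy, *C. difficile* enteritis, some procedural events and an open item for anything else.

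**The concern.** A comparison of harm between arms needs a case definition that can be applied in the same way to every patient, whatever the allocation. Here the definition refers to the content of the intervention. A person who follows 8.2 to the letter would record vancomycin nephrotoxicity in an intervention patient whose consult advised vancomycin. The same person would have no ground to record it in a control patient given the same drug, because nobody recommended anything to that patient's physician under the study.

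Blinding does not protect against this. Treating physicians know the arm (4.2), and group allocation is entered in the CRF (10.3.2.1). The judgement that an event is or is not related to a recommended measure is therefore made with knowledge of the arm.

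What is at stake is the credibility of any statement that the consult was as safe as standard care. A one-sided rule would tend to add events to the intervention arm. In practice, however, recorders may ignore the wording, so the net effect cannot be foreseen.

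**Working it through.** The plan states no figure on this point, so the main check sets the passages side by side.

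1. *What is to be compared?* Safety with the consult against safety without it (1.4). The quantity must therefore be measurable in both arms.
2. *What is a complication?* An event related to a measure recommended in the consultation (8.2). Sections 8.1 and 8.3 also speak of recommended measures.
3. *Does a recommendation exist in each arm?* Yes in the intervention arm, by telephone and then by fax with a therapy proposal. No in the control arm, where both steps are omitted (7.1).
4. *Does another passage override the definition?* Section 8.3 asks for all complications to be charted and transferred to the CRF, but complications there still carry the meaning given in 8.2. The list in 10.3.2.16 carries no consult condition and can be completed for any patient. It does not say that it replaces 8.2.

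Steps 2 and 3 together leave the control arm without a usable definition on a literal reading. Step 4 softens this in practice but does not resolve it.

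**Organ-failure items.** All 4 of the 4 named renal and liver failure items depend on a drug. Elsewhere, renal dysfunction regardless of drug is recorded within 7 days of the first positive blood culture (10.3.2.8). Creatinine, bilirubin and transaminases are recorded on the day of the positive culture only (10.3.2.14). No drug-independent liver failure item is listed. Section 8.1 names contrast-induced renal insufficiency, but the list names only contrast allergy. Such an event would have to go into the open item, the discharge complications field, or the follow-up fields for readmission and new complaints.

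**Can a size be given?** Only under assumptions. Suppose renal failure were equally frequent in both arms and unrelated to the drug. The ratio of counts recorded under vancomycin would then equal the ratio of vancomycin use:
- assumed use 10% (intervention) against 30% (control): 0.10/0.30 = 0.33
- assumed use 30% against 30%: 1.0
- assumed use 40% against 20%: 0.40/0.20 = 2.0

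The protocol gives no use rates, so the result may fall on either side of 1. The assumption also removes any nephrotoxicity of the drug itself. The figures show a mechanism and do not estimate anything.

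**Precision of an any-cause comparison.** With 15 centers × 15 patients = 225 per arm and a common assumed rate p, the 95% half-width for the difference is 1.96 × √(2p(1−p)/225), ignoring clustering:
- p = 5%: 1.96 × √(2 × 0.05 × 0.95/225) = 4.0 points
- p = 10%: 1.96 × √(2 × 0.10 × 0.90/225) = 5.5 points
- p = 20%: 1.96 × √(2 × 0.20 × 0.80/225) = 7.4 points

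Such a comparison could only be descriptive.

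**The case against.** **Recommended measures may mean a class of measures.** Section 8.2 goes on to speak of drugs and measures that are to be recommended and calls the measures routine; 7.5 and 8.1 say the same. On that reading a control patient who receives one of them is covered. The CRF list names drugs and procedures without asking whether a consult advised them, and the study nurse extracts the data from the charts. This reading is possible and may well describe what happens. It does not remove the point, because 8.2 refers expressly to what was recommended in the consultation and no other passage overrides it. The ambiguity lies in a stated rule, so it is not a detail properly left to a later document.

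**No complication analysis is specified.** This is correct. Safety appears as an objective in the synopsis only, and its tabulation may be in an analysis plan that is not shown. This limits the weight of the point. It does not repair the definition, since an analysis plan cannot restore events that were never collected.

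**Recording drug-attributed harm is a legitimate choice.** This stands. Organ failure caused by the infection is disease progression, which is covered by the endpoints on sepsis or septic shock and on mortality. If the consult changes vancomycin use, the resulting change in vancomycin toxicity is a real effect of the intervention. A reader might infer that the drug-named items are wrong in themselves, or that renal and liver failure from other causes go unrecorded. The documents do not support that: open fields exist, and neither the CRF form nor the study manual is shown. A reader might also subtract the 7-day renal window from the 90-day complication window and call the remainder unobserved. The two periods start at different points (blood culture and inclusion), and a share of days is not a share of events.

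**Conclusion.** The point holds for the definition. As worded in 8.1 to 8.3, complications depend on a recommendation that exists in one arm only, and this cannot support the comparison with standard care set out in the synopsis. The conclusion rests on the literal wording of 8.2. If the sites in fact record complications of any routine measure in both arms, the defect is one of text and the data are sound.

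The drug-specific organ-failure items are a matter of completeness and not an error. The one concrete gap is that the contrast-induced renal insufficiency mentioned in 8.1 has no named item.

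The consequence is small. It concerns a supporting, descriptive safety comparison. The primary endpoint, the sample size and the power are unaffected, and all-cause mortality at 30 and 90 days captures fatal harm equally in both arms. The protocol does not allow the size or direction of any distortion to be given. The change is an optional improvement, worth making because it costs little.

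**What to change.** **Sections 8.1 to 8.3.** Define complications as events possibly related to any diagnostic or therapeutic measure for *S. aureus* bacteremia, whether or not a consult recommended it. State that they are recorded identically in both arms over the 90-day window. This costs a few reworded sentences.

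**Section 10.3.2.16, as an addition.** Record acute renal failure and acute liver failure once each, from any cause, with a sub-field for suspected cause: vancomycin, aminoglycoside, contrast medium, flucloxacillin, rifampicin, other. This keeps the drug-specific information and gives contrast-induced renal insufficiency a named place. Report rates by arm descriptively, with confidence intervals.

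The addition needs a small CRF revision and has two drawbacks. Any-cause rates include organ failure from the infection itself and are therefore less specific to the measures. Capture after discharge will stay incomplete, because no visits are planned and follow-up is by telephone.
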